### Outcomes at one and two years’ corrected age (both preterm and term infants)

At one and two years’ CA families will be contacted to participate in follow-up. The child will have a developmental assessment, both parents will be asked to participate (separately) in a parent–child interaction task, and both parents will be asked to complete a set of questionnaires.

#### Developmental assessment

A range of developmental outcomes will be assessed at one and two years’ CA by a blinded assessor (Table 2). At one year, motor development will be assessed by the Alberta Infant Motor Scale (AIMS) [49] and the Neuro-Sensory Motor Developmental Assessment (NSMDA) [50], neurological outcomes with the Touwen Infant Neurological Examination (TINE) [51] and oral motor development with the Schedule for Oral Motor Assessment (SOMA) [52] (Table 2). The AIMS, NSMDA and TINE will be administered by a physiotherapist or occupational therapist and will take approximately 30 minutes. For the SOMA, infants will be seated in a high chair and food and fluid trials will be offered by a research nurse trained in the procedure or by a speech-language pathologist using the standard administration approach. Infants will only be offered food categories that they are currently managing in the home environment. Parents will be instructed to use the standard administration approach in instances where infants refuse to eat for the research nurse or speech pathologist. The SOMA takes approximately 20 minutes to administer and will be videotaped for later rating of the infants’ oral-motor skills by a speech-language pathologist who is blinded to the child’s clinical history.

**Table 2 T2:** Description and purpose of neurodevelopmental assessments

**Assessment**	**Purpose**
AIMS [49]	The *Alberta Infant Motor Scale* (AIMS) is an observational norm-referenced assessment that measures infant motor development between 0 to 18 months of age. There are 58 items across the four positional subscales of prone, supine, sit and stand. The infants least and most mature item in each subscale is identified and marked as observed, then a window is created to assess the items in between as either observed or not observed. Subscale scores are added to obtain a total score. This assessment has been used extensively in follow-up of preterm infants and has excellent psychometric properties [53].
NSMDA [50]	The *Neuro-Sensory Motor Developmental Assessment* (NSMDA) is a criterion-referenced assessment tool constructed to measure neurodevelopment between 1 month and 6 years of age. The five domains of neurological, postural, sensory, fine, and gross motor are summed to create a total NSMDA score. A functional grade is also given for each domain and totalled to provide a total functional grade of normal, minimal deviation, mild deviation, moderate deviation, severe deviation or profound deviation. The NSDMA has good predictive validity for long term motor development [54].
TINE [51]	The *Touwen Infant Neurological Examination* (TINE) is a neurological examination designed for use with infants post term age. There are five clusters of dysfunction assessed – reaching and grasping, gross motor development, brainstem, visuomotor and sensorimotor. The number of criteria fulfilled is recorded for each cluster with an overall dysfunctional cluster rating of yes or no determined. The number of dysfunctional clusters are then added together to determine a neurological classification of neurologically normal, normal sub-optimal, MND (minor neurological dysfunction) or abnormal. The TINE has been shown to predict both minor and major neurological dysfunction in at risk populations including preterm infants [55].
SOMA [52]	The *Schedule for Oral Motor Assessment (SOMA)* is a standardised and psychometrically robust measure of oral-motor skills for eating and drinking for infants aged 8 months to 2 years. It was designed primarily to assess a wide range of oral-motor skills in infants with a grossly intact neurological system.
Bayley-III [56]	The *Bayley Scales of Infant and Toddler Development 3*^ *rd* ^*edition* (*Bayley-III)* is a norm referenced developmental scale of cognitive, language and motor development that has good psychometric properties when used with a local control group, and has been used extensively in the follow-up of preterm infants [53,57].

At two years’ CA, development will be assessed using the Bayley Scales of Infant and Toddler Development – 3^rd^ edition (Bayley-III) [56]. A neurological paediatric assessment will also be performed by a trained paediatrician to assess for cerebral palsy, as well as other sensory problems, such as blindness or deafness. The assessment at two years will take approximately 2 hours.

#### Parent–child relationship assessment

The parent–child relationship for both preterm and term born infants will be assessed using the Emotional Availability Scales (EAS) 4^th^ edition [58]. The EAS is an observational measure examining the contribution of the parent and the child to the parent–child relationship in terms of their emotional responsiveness and attunement to the other member of the dyad. The measure consists of six global emotional availability dimensions – adult sensitivity, adult structuring, adult non-intrusiveness, adult non-hostility, child responsiveness and child initiation. Parents and children will be videotaped in semi-structured play interactions for approximately 15 minutes. The interactions will be coded at a later time by fully trained and accredited coders. The EAS has been used widely with different populations and has evidence of good reliability and validity. For example, the EAS has been associated with other measures of attachment in the parent–child relationship [59] and child development [60], and is reliable across contexts [61].

Table 3 provides an overview of the child assessments and parent-child interaction assessments to be collected over the first two years.

**Table 3 T3:** Administration timetable for infant assessments

	**Birth**	**Up to 32wk***	**32wk to term****	**Term**	**12mth (CA)**	**24mth (CA)**
Neurobehavioural assessment	√	√	√	√√		
Perinatal data	√√					
MRI				√√		
Motor assessment – AIMS and NSMDA					√√	
Clinical feeding assessment - SOMA					√√	
Developmental assessment – Bayley III						√√
Parent–child relationship assessment- EAS					√√	√√
Neurological and Paediatric assessment						√√

*weekly assessments; **fortnightly assessments; √√ = both preterm and term-controls; √ = preterm only; MRI = Magnetic resonance imaging; AIMS = Alberta Infant Motor Scale; NSMDA = Neuro-Sensory Motor Developmental Assessment; SOMA = Schedule for Oral Motor Assessment ; Emotional Availability Scales.

#### Parental assessment

Parent questionnaires will be collected at multiple time points. The first will be when their infant has their first neurobehavioural assessment. Both parents will then be asked to complete questionnaires fortnightly until term equivalent age, at term equivalent age, at three and six months, and at six-monthly intervals until the child’s second birthday (CA). The questionnaires at 3, 6 and 18 months will be posted to families, and asked to be returned to the investigators in a prepaid envelope. Parents will be sent text messages as a reminder to complete questionnaires. The term, one and two year questionnaires will be completed at the time of the infant’s follow-up assessments. Not all measures will be collected at all time points. Each questionnaire to be used in the study is described in Table 4. The time taken to complete these questionnaires will vary from 5 minutes at earlier ages to approximately 2 hours (total) at 24 months’ CA.

**Table 4 T4:** Description and purpose of parental questionnaires

**Assessment**	**Purpose**
CES-D	The *Centre for Epidemiological Studies Depression Scale (CES-D)*[62] will be used to measure depressive symptoms. The questionnaire consists of 20 questions (total score range 0 to 60) with higher scores representing greater depressive symptoms. A score ≥16 on the CES-D represents significant depressive symptoms. This threshold has been shown to correlate well with clinician ratings of depression [63]. The CES-D has been used extensively in general populations and has been used with parents of preterm infants [64,65].
HADS	The *Hospital Anxiety and Depression Scale (HADS)*[66] will be used to assess anxiety. The HADS assesses symptoms of anxiety and depression using 7 items for each scale that are scored with a 4-point rating scale (total score range 0 to 21). Scores above 11 are considered to indicate significant symptoms of depression or anxiety. The HADS has been validated in a variety of settings and has been found to perform well in assessing the severity of anxiety disorders and depression, not only in primary care patients and the general population [67] but also in parents of preterm infants [68].
PCL-S	The *Posttraumatic Stress Disorder Checklist Specific Version*[69] (PCL-S) will be used to assess symptoms of posttraumatic stress disorder (PTSD). The PCL-S consists of 17 items (total score range 17 to 85). The questions are asked in relation to a nominated specific traumatic event, in this case, the birth of their very preterm infant. There is evidence for good test-retest reliability, internal consistency and convergent validity [70]. Only parents of preterm infants will complete the PCL-S.
IPIP-NEO	Neuroticism, or negative affectivity, will be measured with the 10-item Neuroticism scale of the *International Personality Item Pool Five Factor Personality Inventory* (IPIP-NEO) [71]. The Neuroticism scale selected for the present study is from a 50-item self-report version of the NEO PI-R, named the IPIP-NEO [72]. Responses on the Neuroticism scale are scored on a 5-point scale.
PSOC	The *Parenting Sense of Competence Scale* (PSOC) assesses parental satisfaction and efficacy in the parenting role, with higher scores representing higher satisfaction and efficacy in parenting. It is a 16 self-report measure with each item rated by parents on a 6-point rating scale. The PSOC has been widely used and there is good evidence for the validity of the measure [73].
CISS	The *Coping Inventory of Stressful Situations* (CISS) is a 48-item inventory which will be used to measure three major types of coping styles in an individual, including Task-Oriented (problem-solving), Emotion-Oriented (focuses on consequent emotions, becoming angry/upset), and Avoidance Coping (distraction and social diversion) [74]. Parents will be asked to rate each item on a 5-point scale ranging from (1) “not at all” to (5) “very much”.
PSI-LSS	The *Life Stress Scale* from the *Parenting Stress Index (PSI-LSS)*[75] assesses how many of 19 significant life events have occurred for parents within the last 12 months such as divorce, went deeply into debt, entered new school.
Demographic & family questionnaire	Items include relationship to child, whether the parent is the primary caregiver, number of other children in the home, cultural background.
Parent mental health history questionnaire	Five items will assess parental cigarette, alcohol and recreational drug use, and mental health service access history.
Parenting practices questionnaire	The *Parenting Practices Questionnaire* is a 16-item measure that assesses parental warmth, hostility and involvement with their child (Longitudinal Study of Australian Children, LSAC).
ITSEA	The *Infant Toddler Social and Emotional Assessment*[76] (ITSEA) is a 135 item parental report measure of social–emotional problems and competencies in 1 to 3 year olds. It assesses 4 broad domains of behaviour: dysregulation, externalizing, internalizing and competencies. Mean scores below the 10^th^ percentile for competence, or above the 90^th^ percentile for externalising, internalising and dysregulation suggest the infant may be at risk for psychopathology. The ITSEA has good internal consistency, validity, and test-retest reliability, and has been used extensively, including with very preterm populations.
MacArthur CDI	The *MacArthur-Bates Communicative Development Inventories (CDI)*[77] are standardised parent report forms for assessing early language (semantic and grammatical) development in 16 to 30 month old children. The CDI: Words and Sentences (Toddler form) will be completed by the primary care-giver.
FAD	The *Family Assessment Device (FAD)*[78] requires the primary caregiver to indicate whether they “strongly agree”, “agree”, “disagree”, or “strongly disagree” with 60 statements about family functioning. The inventory yields 7 scales: problem solving, communication, roles, affective responsiveness, affective involvement, behaviour control and general functioning. Higher scores indicate poorer family functioning.
ITSP	The *Infant/Toddler Sensory Profile Questionnaire* (ITSP) [79] consists of 48 questions, addressing 6 sensory processing sections, including: Auditory, Visual, Tactile, Vestibular, and Oral Sensory Processing, as well as a General measure. Questions within each sensory processing section yield information about how the child responds to stimuli in each sensory system. Its purpose is to evaluate the possible contributions of sensory processing to the child’s daily performance patterns, to provide information about his or her tendencies to respond to stimuli and to identify which sensory systems are likely to be contributing to or creating barriers to functional performance. The ITSP has excellent content validity and adequate to excellent reliability [80].
CSBS-DP	The *Infant-Toddler checklist* from the *Communication and Symbolic Behavior Scales Developmental Profile* (CSBS-DP) [81] is a 24 item screening tool designed to measure 7 predictors of language including emotion and eye gaze, communication, gestures, sounds, words, understanding and object use in children aged between 6 and 24 months of age.
Social Risk Index	A *Social Risk Index* (family demographic questionnaire) [37] score will be calculated based on a combination of family structure, education of primary caregiver, employment of primary income earner, language spoken at home and maternal age at the birth of the child. Higher scores indicate higher social risk.

Table 5 provides an overview of the questionnaire measures to be collected at each time point. For term-born infants, birth and term are the same time point in Table 5.

**Table 5 T5:** Administration timetable for parent completed questionnaires

	**Birth**	**F/night***	**Term**	**3mth (CA)**	**6mth (CA)**	**12mth (CA)**	**18mth (CA)**	**24mth (CA)**
CES-D	√	√	√√	√√	√√	√√	√√	√√
HADS	√	√	√√	√√	√√	√√	√√	√√
PCL-S			√			√		√
IPIP-NEO	√							
PSOC					√√	√√		√√
PSI-LSS	√√					√√		√√
CISS	√√				√√			
Demographic & family questionnaire	√√							
Parent mental health history questionnaire			√√			√√		√√
Parenting practices					√√	√√		√√
ITSEA						√√		√√
MacArthur CDI								√√
FAD								√√
ITSP								√√
CSBS-DP								√√
Social Risk Index	√√					√√		√√

Note. *F/night = administered fortnightly from first neurobehavioural assessment until term equivalent age; √√ = both preterm and term-controls; √ = preterm only; CES-D = Centre for Epidemiological Studies Depression Scale; HADS = Hospital Anxiety and Depression Scale; IPIP-NEO = International Personality Item Pool Five Factor Personality Inventory-NEO, PCL-S = Posttraumatic Stress Disorder Checklist Specific Version; CISS = Coping Inventory for Stressful Situations; PSOC = Parenting Sense of Competence Scale; PSI-LSS = Parenting Stress Index – Life Stress Scale; ITSEA = Infant-Toddler Social and Emotional Assessment, MacArthur CDI = MacArthur Communicative Development Inventories, FAD = Family Assessment Device, ITSP = Infant Toddler Sensory Profile, CSBS – DP = Communication and Symbolic Behavior Scales Developmental Profiles.

#### Data collection & analysis

The data will be analysed according to the following main aims:

1. To describe the longitudinal evolution of early neurobehavioural development in very preterm infants (<30 weeks’ GA), from birth to two years CA the mean and 95% confidence intervals (CI) for the neurobehavioural assessment will be presented by week up to 32 weeks’ gestation, then fortnightly from 32 weeks’ gestation to term equivalent age, as well as at 1 and 2 years corrected age. Data will be presented according to both gestational and chronological age. Trends over time (according to both chronological and gestational age) will be explored using a mixed effects regression model for each outcome fitted to the continuous age measurement with a fixed effect of time (age) and a random effect for individuals to allow for the repeated observations on each infant.

2. To explore whether the neurobehavioural trajectory varies according to MR findings at term, qualitative MRI variables of interest will be dichotomised into two distinct categories (moderate to severe vs. none or mild white matter injury). The mean (and 95% CI) scores for the neurobehavioural development outcomes at each time point (as described for aim 1) will be plotted separately for children within each category. The change in neurobehavioural development over time (according to both chronological and gestational age) will be modelled using separate mixed effect regression models for each of the neurodevelopmental scores with a fixed effect of time (age) an indicator for moderate-severe injury and an interaction between time and the injury indicator, to assess whether the effect of time is different in those with a moderate-severe injury compared with those with no or a mild injury. The association between early neurobehavioural development and quantitative MRI (e.g. volumes, diffusion, metabolites such as NAA and cho) will be analysed using linear (continuous outcomes) and logistic (binary impairment outcomes) fitting a separate regression model for each outcome and neurobehaviour time point (according to both chronological and gestational age).

3. The validity of early neurobehavioural assessments from birth to term-equivalent age for predicting development at one and two years’ CA in very preterm children will be investigated using separate linear (continuous outcomes) and logistic (binary impairment outcomes) regression models for each neurobehavioural assessment time point according to chronological and gestational age and each outcome. Estimates of the regression coefficients and the R^2^ values (representing the proportion of variability in the outcome explained by the model) from these models will be compared with estimates from the same models using neurobehaviour at term equivalent age as the predictor to obtain an idea of the predictive ability of these early measurements compared with the measurements at term as used currently. Data from term-born controls will be used to provide a local-reference population for calculation of mild, moderate and severe developmental impairment (mild = more than 1 SD below the mean, moderate = more than 2 SD below the mean, severe = more than 3 SD below the mean on the Cognitive Composite Scale on the Bayley-III).

4. To examine symptoms of depression, anxiety, and post-traumatic stress in mothers and fathers of very preterm children at birth during the first two years of the child’s life compared with term-born controls, we will present means and 95% CI for each parental assessment at each time point. For each time point, the observation closest to the specified time for the completed week within +/− 3.5 days for weekly assessment and +/− 7 days for fortnightly assessments will be selected for each individual.

5. To examine the relationships between parental psychological wellbeing, parent and family factors, and very preterm children’s neurobehavioural development at birth, and later two year-old cognitive, motor and social-emotional developmental outcomes, we will fit separate linear regression models for each of the two year outcomes. Initially each parent and child factor will be explored using separate univariable models for each outcome before combining important factors into a single model for each outcome to assess independent predictors.

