## Background

Improving medical technologies are assisting younger and smaller preterm infants to survive. Very preterm infants (defined as born at <32 weeks’ gestation) are at risk of long-term neurodevelopmental problems including cognitive, motor and behavioural impairments [1]. The most immature infants are at the greatest risk for later neurodevelopmental deficits, yet it is these infants whose early neonatal neurobehavioural development we understand the least. In particular, there is a lack of knowledge surrounding early neurobehavioural trajectories between birth and term equivalent age. Nor do we currently understand the relationships that altered neurobehavioural trajectories may have with other important factors such as perinatal complications, cerebral structure, and later developmental outcomes [2].

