### Assessment at term equivalent age (both preterm and term infants)

#### Serial neurobehavioural assessments

At term equivalent age (38–44 weeks’ GA) infants will have neurobehavioural assessments carried out by an independent assessor blinded to previous examination results and clinical history (including prematurity). The term neurobehavioural assessment will consist of the NNNS, followed by the additional items needed to complete the HNNE (i.e. reflexes, arm and leg recoil) and five minutes of video footage for GMs of the infant in an active or quiet alert state.

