#### Magnetic resonance

The MRI scan is not a compulsory component of the study and parents consenting to the study can choose for their baby not to have the MRI scan. For those who consent, MRI scans will be performed without anaesthesia or sedation, between 38–44 weeks’ GA on the same day as the term equivalent age neurobehavioural assessment. All scans will be performed at the Royal Children’s Hospital using the 3 T Siemens Magnetom Trio MRI scanner. The scanning session will take approximately 60 minutes. A full anatomic, functional, developmental and metabolic infant brain MRI study will be performed using the following sequences:

•**T2-weighted images:** Transverse Restore turbo spin echo imaging: Flip angle = 120, Repetition Time = 8910 ms, Echo Time = 152 ms, Field Of View = 192 × 192 mm, Matrix = 192 × 192, 1 mm [3] isotropic voxels.

•**T1-weighted images:** Transverse multi-planar reconstruction imaging with noise suppression: Flip angle = 9°, Repetition Time = 2100 ms, Echo Time = 3.39 ms, Field Of View = 192 × 192 mm, Matrix = 192 × 192, 1.0 mm [3] isotropic voxels.

•**Diffusion weighted imaging:** Transverse echo planar imaging: Repetition Time = 20400 ms, Echo Time =120 ms, Field Of View =173 × 173 mm, Matrix = 144 × 144, 1.2 mm [3] isotropic voxels, 45 gradient directions (range b = 100 to b = 1200s/mm [2]), 3 b = 0 s/mm [2].

•**Resting state functional connectivity MRI:** Transverse 2D echo planar imaging with prospective acquisition correction: Repetition Time = 2910 ms, Echo Time = 28 ms, flip angle = 90°, Field Of View = 151 × 151 mm, Matrix = 64 × 64, 2.4 mm [3] isotropic voxels.

•**Proton magnetic resonance spectroscopy:** Transverse spin echo chemical shift imaging: Repetition Time = 2000, Echo Time = 135, flip angle = 90°, scan resolution = 12 × 12, interpolated 16 × 16, field of view = 103 × 125 mm, voxel size = 10.4 × 8.6 × 15.0 mm.

The MRI scans will be qualitatively evaluated by two independent investigators who are blinded to the clinical neurobehavioural assessment, utilising an established scoring method for newborn infants [42]. This scoring system provides an overall measure of the presence and severity of white matter, cortical grey matter, deep grey matter and cerebellar abnormalities (recorded as normal, mild, moderate, or severe). Quantitative image analysis will involve the following image analyses:

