### Sample size

A sample of 150 very preterm infants and 150 term-born controls was chosen based upon projected workload, the number of infants <30 weeks cared for each year at the Royal Women’s Hospital, and the expected consent rate for the study from families. A sample of 150 infants will enable us to estimate the mean of any neurobehavioural measure employed in this research at any time point to within +/−0.16 standard deviations (based on a 2-sided 95% confidence interval, Aim 1), and to identify correlations between observations as small as 0.2 (Aims 2 and 3), with 80% power (based on 5% significance).

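### Aim 3 compares early and term scores without fixing the set of infants, and neither Aim 2 nor Aim 3 names gestation at birth in its models

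*Protocol article*

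**What the plan says.** **Aim 3** (protocol article, Data collection & analysis). Prediction of one- and two-year development is studied "using separate linear (continuous outcomes) and logistic (binary impairment outcomes) regression models for each neurobehavioural assessment time point according to chronological and gestational age", with a separate fit for every outcome. The comparison of R² is described thus: "values (representing the proportion of variability in the outcome explained by the model) from these models will be compared with estimates". Those estimates are obtained by refitting with the term-age score as predictor, and coefficients are compared in the same way. The stated purpose is a rough view of how early measurements predict relative to current practice at term. No covariate is named, and nothing limits the comparison to infants who have both scores.

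**Aim 2** (same section). The quantitative MRI analysis uses one model per outcome and time point, also with no covariate named. The mixed models for white matter injury list age, injury and their interaction. Aim 2 compares no R².

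**Schedule and instruments.** Families are approached in the first or second week of life (Recruitment). Assessments run weekly from enrolment to 32 weeks, then fortnightly until term or discharge. Before 30 weeks they are mainly observational, and some NNNS and HNNE items are left out or modified at earlier ages (Serial neurobehavioural assessments up to term). At term, "The term neurobehavioural assessment will consist of the NNNS, followed by the additional items needed to complete the HNNE", with video for general movements, anywhere between 38 and 44 weeks. The scan is done "on the same day as the term equivalent age neurobehavioural assessment".

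**Gestation.** Gestation at birth is collected (Perinatal data collection). The Background says: "The most immature infants are at the greatest risk for later neurodevelopmental deficits".

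**Sample size.** The article states: "A sample of 150 infants will enable us to estimate the mean of any neurobehavioural measure". The precision is 0.16 SD, expressed as "standard deviations (based on a 2-sided 95% confidence interval, Aim 1". For correlations, the target reads: "to identify correlations between observations as small as 0.2 (Aims 2 and 3), with 80% power (based on 5% significance".

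**The concern.** The Background wants early examinations to separate normal from abnormal development and to trigger intervention. That requires a score that tells clinicians something beyond gestation, which they know from day one. The protocol describes neurobehaviour as maturing rapidly and the most immature infants as being at greatest risk, so a score may track outcome largely because it tracks gestation. With no gestation term, the planned models cannot tell these two situations apart.

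The early-versus-term comparison has a separate difficulty. If R² differs between 26 weeks and term, the cause could be the timing of the examination, a different group of infants, or a different set of items. The plan as written does not separate these.

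Aim 2 asks about association with brain structure, not prediction. There gestation at birth is an ordinary confounder of score and MRI measure.

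**Working it through.** **1. The plan's own figures.** Inputs: n = 150, r = 0.2, 80% power, 5% significance, 95% interval (Sample size).
- Half-width: 1.96/√150 = 0.160 SD. This reproduces.
- Correlation, Fisher z: n = ((z_α + z_power)/atanh(0.2))² + 3, with atanh(0.2) = 0.2027. One-sided: (2.487/0.2027)² + 3 ≈ 153.4, so 154 infants, and power 0.79 at 150. Two-sided: (2.802/0.2027)² + 3 ≈ 194 infants, power 0.69 at 150, detectable r 0.227.

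The figure 0.2 therefore reproduces closely one-sided. Two-sided it is 0.2 only to one decimal. The article does not state sidedness for it. That is a separate matter; 0.2 is used below as the design target.

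**2. Is gestation at birth held fixed by fitting per time point?** Gestation at birth = gestational age at assessment − chronological age. At a fixed chronological age, maturity at examination is gestation at birth plus a constant. At a fixed gestational week all infants have the same maturity, so that link disappears, but gestation at birth still varies. Neither scale alone fixes it.

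**3. A score with nothing beyond gestation.** Then r(score, outcome) = r(score, gestation) × r(outcome, gestation). Chance of significance at n = 150: Φ(atanh(r)·√147 − 1.96). The documents give no such correlations, so these are assumed:

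| r(score, gestation) | r(outcome, gestation) 0.2 | 0.3 | 0.4 |
|---|---|---|---|
| 0.3 | 0.06 (11%) | 0.09 (19%) | 0.12 (31%) |
| 0.5 | 0.10 (23%) | 0.15 (45%) | 0.20 (69%) |
| 0.7 | 0.14 (40%) | 0.21 (73%) | 0.28 (94%) |

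R² runs from 0.004 to 0.08. The larger values apply mainly to the chronological-age models.

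**4. Different infants, same relation.** Assume gestation uniform on 24–30 weeks, standardised to g. Score s = a·g + noise of variance 1 − a². Outcome y = b·g + 0.3·(s − a·g) + noise of variance 1 − b². In infants born before 27 weeks, var(g) falls from 1 to v = 0.25. Then

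R² = [abv + 0.3(1 − a²)]² / {[a²v + 1 − a²]·[b²v + 0.09(1 − a²) + 1 − b²]}.
- a = 0.5, b = 0.3, all infants: 0.375²/1.0675 = 0.132. Born <27 weeks: 0.2625²/(0.8125 × 1.000) = 0.085.
- a = 0.7, b = 0.4, all infants: 0.433²/1.0459 = 0.179. Born <27 weeks: 0.223²/(0.6325 × 0.9259) = 0.085.

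R² falls by a third to a half with no change in how the score works.

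**5. R² in logistic models.** In simulated data with a linear R² of 0.10, three common versions (McFadden, Cox–Snell, Nagelkerke) give 0.053, 0.045 and 0.078 when impairment is cut at −1 SD, and 0.062, 0.013 and 0.068 at −2 SD. None is the share of variability explained. The values depend on the version and on how common impairment is, which may differ between groups of infants.

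**6. Age at the term visit.** The window is 44 − 38 = 6 weeks. If timing were uniform (assumed), the SD of age would be 6/√12 = 1.73 weeks, shared by score and scan.

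**7. Price of the changes.** One covariate replaces n − 3 by n − 4: detectable r = tanh(2.802/√147) = 0.227 becomes tanh(2.802/√146) = 0.228 (partial r, two-sided). Correlation of 0.5–0.7 between score and gestation also multiplies the variance of the score coefficient by 1/(1 − 0.25) = 1.33 to 1/(1 − 0.49) = 1.96, before any gain from lower residual variance. If only 120, 100, 75 or 50 infants (assumed) have both scores, detectable r is 0.25, 0.28, 0.32 or 0.39.

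**The case against.** **Prediction needs no adjustment.** Aim 3 asks how well early scores predict compared with term scores, and an unadjusted model is legitimate for that. This stands. A reader might infer that the predictive-validity results are invalid or confounded; the documents do not support that. What the models lack is evidence of value beyond gestation. The defence does not reach Aim 2.

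**Age is already handled.** A reader might infer that age at assessment is ignored. It is not: models are fitted per time point on both age scales. What remains is age within the wide term window, shared by score and scan, and this concerns the term time point. For earlier scores, age at scan is not shared with the score.

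**R² is compared like with like.** A reader might think R² is compared between linear and logistic models, or in Aim 2. The text supports neither. Only the interpretation given for R² fails in the logistic models.

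**Premie-Neuro has no term value.** This is by design. Table 1 gives its range as 23–37 weeks, and the comparator is term neurobehaviour, not necessarily the same tool.

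**This is a condensed article.** Covariates and analysis sets may sit in an analysis plan not shown. That is possible. However, the article fixes predictor, outcome, model type and comparator for Aim 3, lists the fixed effects of its mixed models, and for Aim 5 plans a combined model to find independent predictors. Aim 3 has no such step.

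**The sizes are assumed.** True. At the low end (r = 0.06) the effect is negligible.

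**Conclusion.** The point holds in a limited form. Followed as written, Aim 3 compares early and term R² and coefficients in sets of infants that the schedule makes different, on item sets that differ, and it cannot show whether a score adds to gestation at birth. Its reading of R² does not apply to the logistic models. Aim 2 leaves gestation at birth unadjusted and, at term, age within the 38–44 week window.

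The size depends on correlations the documents do not give. Over the assumed range, gestation alone produces r of 0.06 to 0.28, which spans the 0.2 target. A changed set of infants alone can take R² from 0.13 or 0.18 to about 0.085. That the sets differ is inferred from the schedule; the article gives no counts per time point. The planned analyses need not be withdrawn, but additions should be made before early scores are described as matching the term examination or as useful beyond gestation.

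**What to change.** Keep the unadjusted models and add:

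1. Gestation at birth in the Aim 2 and Aim 3 models, with incremental R² over gestation reported in Aim 3.
2. Age at scan or assessment in models that use the term score or an MRI measure.
3. The early-versus-term comparison restricted to infants with both assessments, on standardised scores, with a bootstrap confidence interval for the difference and the number of infants at each time point.
4. AUC with a confidence interval for binary impairment, in place of R².

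Gestation at birth is already collected, and age follows from visit dates. The cost is some extra analysis, wider intervals for score coefficients where score and gestation are strongly correlated, and less precision at the earliest time points, where fewer infants have both scores.
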